### Anthropometric Measurements

Height will be measured using a vertical stadiometer (Seca Portable 217, Seca, UK) and will be recorded to the nearest millimetre or one-tenth of a centimetre (0.1 cm). Body weight will be assessed using a digital, electronic weighing scale (Seca 813, Seca, UK). It will be based on the nearest one-tenth of a kilogram (0.1 kg). Body fat composition will be evaluated using a portable body composition analyser (Tanita SC-240 MA, the Netherlands). Waist circumference (WC) and hip circumference (HC) will be measured using a non-elastic Seca measuring tape (Seca 201, Seca, UK), to the nearest millimetre.

### Blood Pressure

The help of two qualified medical officers will assess the blood pressure and pulse rate of the participants. The participants will seat in the upright position with their right upper arm position at the level of the heart with both feet flat on the floor. Systolic and diastolic arterial blood pressure will be obtained using a stethoscope and a mercury sphygmomanometer.

### Outcomes

#### Potential Trial Outcomes

As this is a feasibility study, the focus of the current study will be whether the intervention can be delivered as intended and desired outcomes can be attributed. It is envisaged that if we have to move to a larger trial that the primary outcome will be the participants' consumption of healthy canteen items. The participants will be deemed as consuming healthy canteen items or green foods based on their dietary intake of more than 50% of listed menu items. The canteen operators will be tasked with auditing the green items available for sale at the school canteen. During follow-up, two dietitians will audit the results based on the canteen audit and discussion with canteen staff. Food classification tools and guidelines published by the Ministry of Education in Malaysia will be used to categorise the food (see Table 1).

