Trained dietitians will audit the canteen menu and food items sold by the school canteen and convenience shops in all schools (during the 4-week intervention phase, once a week). The menu audit process has been implemented in other studies (45). The study outcome measures will be assessed at the individual level and will consist of a 3-day diet history assessment and anthropometric measurements that will be conducted at baseline and post-intervention (4 weeks after intervention). Focus group discussions with students who will be involved in the intervention and interviews with teachers, school headmasters, and canteen operators will be conducted post-intervention to explore the acceptability and barriers in implementing the proposed intervention (see Supplementary Material 1). Estimation of sales will be done based on weekly receipts from the canteen and school convenience shop operators of healthy food items, such as vegetables, fruits, and low-calorie *kuih*. The data will be collected at baseline (August to September 2018) and the following intervention will be carried out after 3 months the year after (January to April). The summary of intervention assessment and logic model are shown in Figures 1, 2, respectively.

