### Intervention Overview

This study will explore the feasibility of conducting a dietary intervention in different types of schools (urban or rural) and its potential (evidence of promise) for improving healthy eating practices in adolescents from different socioeconomic backgrounds. It will focus on offering healthy food and beverage options in the school canteen and convenience shop. School canteens will be supposed to support healthy eating based on the healthy canteen guidelines designed by the Ministry of Education (MOE) (52). This will be achieved by increasing the availability and promotion of an extensive range of foods that should make up the majority of a healthy diet (GREEN). AMBER foods can be consumed only sometimes, choosing healthier alternative foods and avoiding large serving sizes that should be eaten in moderation. RED foods are “stop and think foods” that do not meet specified minimum nutrient criteria (RED). The intervention will try to overcome barriers to healthy canteen guidelines implementation and adherence. Specifically, the intervention will assist schools to remove “red-flagged” and “ban” food items from the canteen menu while increasing the availability of “GREEN” menu items. The objective will be to ensure more than 50% of all canteen menu items are in the “GREEN” category. Examples of “GREEN”, “AMBER,” and “RED” food items are indicated in Table 1.

**Table 1 T1:** Food classification description.

	**Everyday foods– “GREEN”**	**Select carefully– “AMBER”**	**Occasional foods– “RED”**
Nutritional quality	• High in nutrients and fibre. • Low in saturated fat and/or added sugar and/or salt.	• Moderate in added fat and/or sugar. • Contribute to excessive kilojoules if consumed in large serving size.	• Very low in nutritional value. • High in saturated fat and/or added sugar and/or added salt.

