## Discussion and Conclusion

The MyHeARTBEaT study proposes the design and rationale for a school-based intervention to facilitate the adoption of a healthy canteen policy in Malaysian schools. The study will try to determine if the audit and subsidisation for healthy foods can improve/increase the availability of the healthy food and drinks option at the school canteen and convenience shop, improve the number of school canteens, which offer healthy food options, increase the number of students who consume greater amounts of fruits and vegetables, and decrease the intake of SSBs by students. This strategy may have the potential to offer cost-effective and sustainable support to improve the school canteen food environment. The insights into the effects of price-related approaches to improve food consumption and purchasing behaviours may provide evidence to build appropriate policy and programme responses to the epidemic of obesity and poor diet quality currently facing Malaysian adolescents (49).

Limited healthy lifestyle school-based interventions were conducted in Malaysia. As such, this study addresses a significant research gap and a potentially valuable missed opportunity in efforts to promote healthy eating behaviours among Malaysian adolescents. The research may contribute to the literature on the adverse effects of poor nutrition and associated adverse health outcomes, including obesity, in the Malaysian population and worldwide. While the impacts of school-based canteen interventions have been examined in other studies in Malaysia, the upcoming trial will be the first to analyse the impact of healthy food subsidisation in Malaysian school canteens and targeting both school convenience shops and canteens for intervention. The intervention will be considered to warrant evaluation via a full trial if the study achieves more than 50% of all healthy canteen menu items in the “GREEN” category and recruits 80% of eligible participants. Based on this feasibility, we shall plan either to use interventions such as training of canteen and school convenience shop operators only (intervention 1) or training with some financial subsidy (intervention 2) for the full trial.

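### The envisaged primary outcome sets a student's intake against the menu list, so read literally it does not measure how much of that student's canteen intake is GREEN

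*Protocol article*

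**What the plan says.** The Potential Trial Outcomes section states that, if a larger trial follows, "the primary outcome will be the participants' consumption of healthy canteen items". It gives one rule for this: students are "deemed as consuming healthy canteen items or green foods based on their dietary intake of more than 50% of listed menu items". The section then turns to auditing the green items on sale and to classifying food with Table 1.

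The same 50% figure appears twice more, both times as a property of the menu:

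- Intervention Overview: "The objective will be to ensure more than 50% of all canteen menu items are in the “GREEN” category".
- Discussion and Conclusion: a full trial is warranted "if the study achieves more than 50% of all healthy canteen menu items in the “GREEN” category and recruits 80% of eligible participants".

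Outcomes are meant to belong to students. Overview of Study Methodology says "The study outcome measures will be assessed at the individual level" and that they "will consist of a 3-day diet history assessment and anthropometric measurements that will be conducted at baseline and post-intervention". Data Collection describes a menu covering everything the canteen sells, snacks and beverages included. The number of items on it is not stated.

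**The concern.** The rule puts what a student ate in the numerator and what the canteen offers in the denominator. That ratio describes how much of the menu a student has sampled, not how healthy the student's choices were. As worded it also sets no colour condition: a student could pass on AMBER and RED items, and one who ate only fruit every day could fail.

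The second objective under Aims is to test whether changes in food choices can be assessed. A candidate primary outcome that does not measure food choice cannot be piloted usefully, and this study's data on it would be a poor basis for planning the full trial.

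**Working it through.** The article gives no expected responder rate or menu length, so there is no figure to reproduce. The check is whether the rule can be met, and which way it moves, under each reading of the sentence.

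**Inputs.** From the article: a 3-day diet history (Overview of Study Methodology, Dietary Assessment) and two main meals provided at school (Introduction). Assumptions, shown as ranges: all three recalled days are school days; menu length M is 10 to 40; the number of canteen items recorded, k, is 6, 9, 12 or 18. With 3 × 2 = 6 school meals, these k correspond to 1, 1.5, 2 and 3 items per meal.

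**Reading 1, literal: more than half of all listed items.** Different items needed = floor(M/2) + 1. The probability of reaching that number is computed for k random draws with replacement, by the recursion P(j distinct after t+1 draws) = P(j after t) × j/M + P(j−1 after t) × (M−j+1)/M. Hand check for M = 10, k = 6, 6 needed: 10×9×8×7×6×5 / 10^6 = 0.151.

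| Menu items | Needed | k = 6 | k = 9 | k = 12 | k = 18 |
|---|---|---|---|---|---|
| 10 | 6 | 0.15 | 0.75 | 0.96 | >0.99 |
| 12 | 7 | impossible | 0.51 | 0.89 | >0.99 |
| 15 | 8 | impossible | 0.29 | 0.80 | >0.99 |
| 20 | 11 | impossible | impossible | 0.12 | 0.88 |
| 30 | 16 | impossible | impossible | impossible | 0.10 |
| 40 | 21 | impossible | impossible | impossible | impossible |

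The entries marked impossible are pure counting (needed exceeds k) and do not depend on random choice. The others are generous, because students who return to favourites record fewer different items.

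The missing colour condition, by example: on a 20-item menu with 8 GREEN items, 20 − 8 = 12 items are not GREEN. A student who eats 11 of those 12 qualifies as a consumer of green foods.

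*Direction under the intervention.* Schools are to "remove “red-flagged” and “ban” food items from the canteen menu while increasing the availability of “GREEN” menu items". From a 20-item menu needing 11:

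- a one-for-one swap of RED for GREEN leaves the requirement at 11;
- adding 10 GREEN and dropping none gives 30 items and a requirement of 16;
- dropping 10 RED and adding 5 GREEN gives 15 items and a requirement of 8.

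**Reading 2: more than half of the GREEN items.** Raising GREEN items from 8 to 15 raises the requirement from 5 to 8. With 9 GREEN items recorded, the probability falls from 0.90 to 0.29. Even if recorded GREEN items rise from 6 to 9 as the list grows, it falls from 0.46 to 0.29; it increases to 0.80 only if they double to 12.

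**Reading 3: each student takes the school's menu share.** Six schools give six values at each assessment. This is availability, not individual intake.

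**Reading 4: more than half of the student's own recorded items are GREEN.** Binomial tail P(X ≥ floor(k/2) + 1), with random choice from a menu of GREEN share g:

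| g | k = 6 | k = 9 |
|---|---|---|
| 30% | 0.07 | 0.10 |
| 50% | 0.34 | 0.50 |
| 60% | 0.54 | 0.73 |
| 70% | 0.74 | 0.90 |

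Only this reading concerns the student's own choices, can be met whatever the menu length, and rises with GREEN availability. It is not what the sentence says.

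**The case against.** The strongest reply is that the sentence is loosely worded rather than wrong. The outcome is named as consumption of healthy items and the surrounding text is about green items and Table 1, so a sympathetic reader would take it as Reading 4. That reading is plausible as the intent. But the article states a rule, and the rule names the menu as its denominator. This is not detail left to a fuller document.

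Three stronger inferences are tempting, and the documents do not support them.

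- *The outcome will be near zero in every arm.* This needs a long menu and few recorded items, and the article gives neither figure. The diet history also covers mid-morning snacks and afternoon tea, and the menu includes beverages, so 12 recorded items is not a ceiling. With 18, a 20-item menu gives 0.88.
- *The bar rises with every GREEN item added.* This holds if the denominator is GREEN items only or if the list grows. It fails if RED items are removed in step, which the intervention also intends.
- *The study's own conclusions are compromised.* The outcome is only envisaged for a later trial. The progression criteria are menu-level GREEN share and recruitment, Sample Size Estimation contains no calculation, and Planned Analysis rules out significance testing. Dietary intake is a separate secondary outcome, and sales receipts and coupon counts are also collected.

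**Conclusion.** The point holds as a defect in the definition of the envisaged primary outcome. A threshold that elsewhere describes the menu has, it appears, been applied to individual intake. Followed literally, the rule has the wrong denominator and no colour condition.

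Its size depends on assumptions. With 9 to 12 items recorded over three school days, qualifying is impossible or rare (0.12 at best) for menus of 20 to 30 or more items, but has probability 0.75 to 0.96 for a 10-item menu. The direction of movement under the intervention is not determined: it depends on whether the denominator is all items or GREEN items, and on whether the list grows. Menu length, items recorded and random choice are all assumed, so the probabilities are illustrative; the mismatch of numerator and denominator does not depend on them.

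Severity is moderate. The definition should be corrected before the outcome is piloted or carried forward, but nothing formal in this study rests on it.

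**What to change.** Define the outcome as the share of the canteen and convenience-shop items (or energy) that each student consumed on diet-history school days that is GREEN under Table 1. State the unit and the time window. If a binary outcome is wanted, use more than 50% GREEN of the student's own intake as the cut-off; a continuous percentage is preferable but optional.

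Keep the menu-level 50% target in Intervention Overview and in Discussion and Conclusion as a separate availability measure, and reconcile the wording of Potential Trial Outcomes with those two sections.

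The cost is small: a change of wording, coding of diet-history foods by colour, and a record of whether each food came from the canteen, the shop or elsewhere. Dietary Assessment does not say that source is captured, so the interview form may need one added field.

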Several initiatives have been implemented in Malaysia and across the world to ensure adherence to established nutritional guidelines and standards, healthy canteen policies, and strategies for all foods served in school canteens (34–36). However, the impact of these programmes and their long-term sustainability are unclear. Addressing this gap is particularly important in Malaysia, where the school is an important provider of two main meals (breakfast and lunch) (37). In a recent systematic review about Malaysian adolescents' dietary intake, there was a small difference in dietary patterns according to ethnic diversity, which indicated that Malays had higher SSBs intake and lower diet quality than Chinese and Indian adolescents (21). Furthermore, Malay adolescents preferred Western-based and local-based dietary patterns while Chinese adolescents intended to follow a healthy-based food pattern, which may reflect the effect of socio-cultural diversity on food preferences (21).

In Malaysia, the schoolchildren purchased food from the canteen and *koperasi* (school convenience shop) which are run by the canteen operators and school administration, respectively. The *koperasi* sells mostly energy-dense snacks and beverages. The staple foods usually was sold at the canteen such as noodles, fried rice, nuggets, and fried chicken, energy-dense traditional cakes (e.g., *Rempeyek, Kuih Peneram, Kerepek Ubi Kayu, Kuih Baulu*, etc.), and SSBs.

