### Data Collection

Data will be collected at baseline and post-intervention. All six eligible governmental schools with an operational canteen will be required to complete baseline data collection. The schools' characteristics, including school size, location, and the number of days the canteen operates, will be captured before randomisation. Furthermore, canteen vendors will be asked to show the serving menu that captures all foods (even snacks and beverages) available for sale at school canteens to the research team before the canteen checklist assessment.

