### Dietary Assessment

A questionnaire will be used to obtain information regarding adolescents' dietary intake. This study will use a validated 3-day diet history to ensure greater accuracy, namely to estimate the respondents' energy intake (16). The tool was pre-tested on 40 participants from two different schools (one school each from rural and urban areas, respectively) (16). Qualified and trained dietitians will conduct an open-ended interview with adolescents to collect information on their food habits through the day (breakfast, mid-morning snacks, lunch, afternoon tea, dinner, and supper). A flip chart will be used as an additional tool to assess the subjects' diet and help estimate their portion size. Nutritionist Pro™ Diet Analysis software will be used to assess the nutritional content of the food (16).

Any misreporting may be heightened in dietary intervention studies. A reliable and valid short form of the Marlowe-Crowne social desirability scale will be administered to identify and control participants prone to these traits (53).

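### The envisaged primary outcome divides a student's intake by the school's menu list, which the intervention itself changes, so the bar can differ by arm with no change in eating

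*Protocol article*

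**What the plan says.** Under Potential Trial Outcomes, the article states that in a larger trial "the primary outcome will be the participants' consumption of healthy canteen items". It turns this into a yes/no classification of each student, who will be "deemed as consuming healthy canteen items or green foods based on their dietary intake of more than 50% of listed menu items". No other section gives a different definition.

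Four other places bear on that rule:

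- **The list.** Under Data Collection, vendors are asked to "show the serving menu that captures all foods (even snacks and beverages) available for sale at school canteens". The number of items is not given.
- **The list changes in intervention schools.** Intervention Overview has the programme remove red-flagged and banned "food items from the canteen menu while increasing the availability of" GREEN items. It sets a menu target with the same cut-off: "The objective will be to ensure more than 50% of all canteen menu items are in the" GREEN category.
- **The list stays as it is in control schools.** The Control section leaves the two control schools' canteens and shops on their usual service.
- **The observation window.** Dietary Assessment says: "This study will use a validated 3-day diet history". The Introduction says that "the school is an important provider of two main meals (breakfast and lunch").

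**The concern.** A measure of what a student chooses should be taken over what that student ate. Here the share is taken over what the school lists. Two things follow.

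First, the intervention acts on the denominator. The list is a target of the programme in four schools and is left alone in two, so the yardstick is not the same across arms. Within an intervention school it need not be the same before and after. A difference in the proportion of students classed as healthy consumers can then reflect the menu and not eating.

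Second, the words do not say that the items counted must be GREEN. On an all-items reading, a student who eats widely from the menu passes whatever the items are.

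Intervention Overview uses the same 50% figure as a target for menu composition. The outcome sentence appears to have merged that school-level availability measure with a student-level intake measure.

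At stake is the second specific objective, testing whether changes in food choice can be assessed, together with any rate or effect size from this outcome that is used to plan a full trial.

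**Working it through.** **Figures in the plan.** The only figure that can be reproduced is the sample size: 6 × 75 = 450 and 6 × 80 = 480, as stated. The point does not depend on it. The 50% cut-off is a definition, so the check asks how it behaves when the list changes.

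**The bar.** With M listed items, more than 50% means at least floor(M/2) + 1 different items.

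| Listed items M | 10 | 14 | 20 | 26 | 30 | 40 |
|---|---|---|---|---|---|---|
| Different items needed | 6 | 8 | 11 | 14 | 16 | 21 |

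**Shift by arm, eating held fixed.**

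- *All-items reading.* If a 20-item menu is cut to 14, the bar falls from 11 to 8, and a student who eats 8 different items changes from no to yes. If it grows to 26, the bar rises to 14. If every RED item is replaced by one GREEN item, M and the bar are unchanged.
- *GREEN-only reading.* If listed GREEN items go from 4 to 12, the bar goes from floor(4/2) + 1 = 3 to floor(12/2) + 1 = 7. A student who eats 3 different GREEN items passes on the shorter list and fails on the longer one.

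**Can the bar be reached in three days?** This needs assumptions, since the article gives neither menu length nor the number of items chosen. Let n be the selections over 3 days:

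- n = 9: 3 occasions × 1 item × 3 days
- n = 12: 2 × 2 × 3
- n = 18: 3 × 2 × 3

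Treat selections as uniform random draws from M items. The chance that the number of distinct items reaches floor(M/2) + 1, from the exact distribution, is:

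| M | Needed | n = 9 | n = 12 | n = 18 |
|---|---|---|---|---|
| 10 | 6 | 75% | 96% | over 99% |
| 12 | 7 | 51% | 89% | over 99% |
| 20 | 11 | impossible | 12% | 88% |
| 24 | 13 | impossible | impossible | 60% |
| 30 | 16 | impossible | impossible | 10% |
| 40 | 21 | impossible | impossible | impossible |

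For the GREEN-only reading, take 12 selections, each GREEN with probability 0.3 and spread evenly over the listed GREEN items. The pass rate is 48.1% with 4 listed GREEN items, 9.6% with 8 and 0.65% with 12. The share of selections that are GREEN is the same throughout.

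**With the student's own intake as denominator.** A student with 5 GREEN items out of 9 eaten scores 5/9 = 56%, above the cut. One with 3 out of 9 scores 33%, below it. Neither result depends on whether the menu lists 14, 20 or 40 items.

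**The case against.** The case on the other side has real substance.

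- **Intention.** The sentence is about students who consume healthy or green foods, and the text around it has green items audited and foods classified by Ministry tools and Table 1. GREEN status was clearly intended, and the authors may have meant that more than half of the items a student eats are GREEN. That stands as a reading of intent, but the words do not say it, and if it was meant, the fix below is what the sentence should say.
- **An unreachable bar.** A reader might infer from the rule that almost nobody could pass. The documents do not support this as a general statement. At 12 items with 12 selections the modelled pass rate is 89%, and at 20 items with 18 selections it is 88%. Impossibility appears only on longer lists or with fewer selections, and uniform random choice is itself an assumption.
- **A certain difference between arms.** A reader might infer that the bar must differ by arm. On the all-items reading it need not: the programme both removes and adds items, and the article does not say whether lists end up shorter, longer or equal.
- **False conclusions from this study.** A reader might infer that the study could wrongly declare success or failure. Planned Analysis rules out formal comparison, significance testing and p-values. The outcome is only envisaged for a later trial. The progression criteria in Discussion and Conclusion are a menu-level GREEN share and 80% recruitment, and neither uses this rule.
- **Link to the full trial.** Sample Size Estimation wants an indication of the likely full-trial size but does not name the outcome it would come from.

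These points limit the consequence. They leave the denominator as stated.

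**Conclusion.** The outcome definition is faulty as written: it takes a student-level share over a school-level list that the intervention alters in four of the six schools. The bar can therefore differ by arm with no change in food choice. On the GREEN-only reading, adding GREEN items raises the bar, so better delivery makes the outcome harder to meet. On the all-items reading, the bar follows list length and a student need not eat GREEN items to pass. This conclusion rests on the text alone.

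The size is illustrative because menu lengths and selections are assumed. The bar moves from 3 to 7 items when listed GREEN items go from 4 to 12. An assumed 40-item menu would require 21 different items, beyond even 18 selections in three days.

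The practical weight is moderate. The defect bears on whether food choice can be assessed and on what a full trial inherits, not on this study's decision to proceed. It is worth correcting because the data needed are already to be collected.

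**What to change.** Under Potential Trial Outcomes, replace the rule with a share of the student's own intake: GREEN canteen and convenience-shop items eaten, divided by all such items that student ate on the recorded days.

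- Classify items by the same Table 1/Ministry scheme in all six schools and at both time points.
- If the cut at more than 50% is kept, apply it to that share.
- Report separately the number of students who ate no canteen or shop items on the recorded days.
- Keep the proportion of listed items that are GREEN as a school-level availability measure only.

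The cost is a short rewording of the outcome definition. It relies on the 3-day diet history and the food classification already planned, provided foods bought at school are identified in the history. The one drawback is that the share is undefined (0/0) for students who ate nothing from the canteen or shop, which is why they need their own line in the report.
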